### Study Setting

This study will be conducted in select remote communities in the Peace River Region of Northern Alberta, located ~1,000 km from Edmonton with a population base of ~75,000 (Figure 1). The CKD population in this region receives care from a primary care network consisting of 35 primary care providers (PCPs) affiliated with 9 primary care group practices. Patients with CKD and hypertension will be identified from the Northern Alberta Renal Program (NARP) database and contacted by the study team to participate in this study.

**Figure 1. fig1-20543581221077500:**
[figure not shown]
Map of Alberta showing Northern Alberta and Peace River region.

### Design, Randomization, and Allocation

We have designed this study as a 2-arm pragmatic RCT comparing the clinical care of remote dwelling hypertensive CKD patients. We will randomly assign the patients with CKD and hypertension to each study arm (1:1) that is, HBPT plus protocol-based case management versus HBPT plus usual care (Figure 2). A randomized permuted block design of 4 and 6 will be used. The random allocation sequence will be computer generated using STATA 17 software (StataCorp. 2021. Stata Statistical Software: Release 17. College Station, Texas: StataCorp LLC) and allocation will be concealed by web-based central randomization using The Research Electronic Data Capture System (REDCap version 8.8.2; 2018 Vanderbilt University). Participants and clinicians will not be blinded to group assignment.

**Figure 2. fig2-20543581221077500:**
[figure not shown]
A summary of the trial design. *Note.* HBPT = home blood pressure telemonitoring; BP = blood pressure; SBP = systolic blood pressure; DBP = diastolic blood pressure; CKD = chronic kidney disease.

### Participant Recruitment

#### Study population

The following eligibility criteria will apply to this study:

Age ≥ 18 years with documented diagnosis of established CKD (not on dialysis with eGFR < 60 mL/min/1.73 m^2^ and/or proteinuria > 1 g/day)Remote dwelling patients in the Peace River region of Alberta, CanadaPatients known with hypertension (physician diagnosed / self reported and currently taking antihypertensive medications)Owning a smartphone (iOS or Android) with access to wireless internet connection.Proficiency in English language (both verbal and written); and ability and willingness to provide informed consent for participation.Ability and willingness to use the HBPT device (≥80% recordings sent in the training period)

The following exclusion criteria will apply to this study:

Patients with hypertensive urgency or emergency identified during the training period (immediate consultation will be initiated with the patient’s PCP or with a hypertension specialist)Patients with stage 5 CKD (eGFR ≤ 15 ml/min/1.73 m)^2^ or patients receiving kidney replacement therapyHeart failure with reduced ejection fractionPresence of any terminal illness (life expectancy < 1 year)Participation in any ongoing clinical drug trialPregnancy, lactation/breastfeedingPlanning to relocate out of the Peace River region or residence in an area without mobile phone coverage.

#### Intervention arm

Due to the ongoing COVID-19 restrictions for face-to-face patient contact, we will train patients through phone and video contact in addition to sending each participant a written information outlining the study procedures, how to measure their BP, how to download and use the Sphygmo App, and how to transmit BP measurements from their smartphones (Supplementary Appendix 1 and 2). Thus, we will train patients to measure BP using guideline recommendations^
10
^ leveraging a locally developed and validated HBPT system (http://mmhg.ca/about-us/). Patients will receive a Bluetooth-enabled and validated electronic upper arm oscillometric BP device (A&D Ltd. UA-651BLE; San Jose, California) that will be paired to their smartphone. Instructions on how to measure appropriate cuff size will also be provided to each patient (Supplementary Appendix 2). Patients will be required to sit with their back rested for at least 5 minutes with the BP cuff around their arm. They will then be required to push the start button on the HBPT device to initiate BP measurement. HBPT values will be based on a series comprised of the mean of duplicate measures, for morning and evening, for a 7-day period and the first day home BP values will not be considered.^
11
^ Thus, mean SBP for the week will be computed from average of duplicate readings for the next 6 days, that is, 24 measurements. The BP data will be auto transmitted via Bluetooth to their smartphone and relayed to a secure web portal for review (Figure 3). This 7-day protocol will be repeated each month until BP is in the required target range. Once BP is controlled, that is, guideline-concordant, the 7-day protocol will be repeated every 3 months for 1 year. The smartphone platform is already established in 4 markets (Canada, United States, Hong Kong, Singapore) and is widely used by members of the target population^
29
^ and a similar system has been tested in a pilot study of 20 patients from the University of Alberta’s Hypertension Clinic as well as in a trial of BP telemonitoring in very elderly patients residing in supportive living environments.^
30
^

**Figure 3. fig3-20543581221077500:**
[figure not shown]
Working prototype of a home BP telemonitoring system. *Note.* BP = blood pressure Intervention / control patients measures BP at home. Information is transferred wirelessly from the BP monitor to the smartphone via a Bluetooth transmission protocol. The smartphone receives the information, organizes, and displays it on the smartphone, and encrypts the information for further transmission over the Internet to a secure server. If necessary, case managers interact with intervention patients for medication adjustments (up / down) via a web portal using a data transmission protocol known as Health Level 7 (HL-7; www.hl7.org). Control patients will take their BP recordings to their primary care physician (PCP) or nurse practitioner (NP) during their routine check-up visits.

Tele-transmitted BP readings will be summarized within the server using telemonitoring software and temporal trends will be plotted. For the active arm of the study, BP data will be tele-transmitted to the study case manager, who will oversee lifestyle modifications and BP self-monitoring and medication adherence. The case manager will also review telemonitored BP summaries, make protocol-based therapeutic adjustments based on a defined algorithm (Figure 4), and send summaries to participants’ PCPs to inform them of treatment changes to facilitate communication between patients and care providers. Medications will be adjusted based on guideline recommendations^10,11^ and existing treatment protocols used in other chronic disease settings (ie, diabetes and stroke).^
31
^ Participants will also receive a document that shows how to unlink their account and delete the Syphmo App from their smartphones at the end of the study (Supplementary Appendix 3).

**Figure 4. fig4-20543581221077500:**
[figure not shown]
Case manager protocol for BP lowering medications. *Note.* A home BP series will consist of a 24-reading average (duplicates measured in the morning and evening) taken over a consecutive 7-day period. Medications will be added in a guideline-concordant manner. We will ensure that all patients are at least on an Angiotensin converting enzyme-inhibitor (ACE-i) and diuretic, unless medically contraindicated. BP = blood pressure.

#### Control arm

Patients in the control arm (usual care) will receive the same HBPT device and BP measurement training as those in the intervention arm and will also follow the same measurement protocol—That is, 2 measurements taken in the morning and 2 taken again in the evening for 7 consecutive days. The values from the first day will be discarded and the mean SBP for the week will be computed from the average of the readings from the following 6 days, that is, 24 measurements. However, the study case manager will not interact with patients in this group. Patients in his group will be expected to inform their PCP or nurse practitioner (NP) of their BP readings at their scheduled consultations. For those in this group whose 6-day average SBP readings are ≥ 220/110 mmHg or <70 mmHg, the case manager will notify the Data Safety and Monitoring Committee (DSMC) for urgent review, treatment plan and referral strategy. Each participant’s PCP / NP will be informed of the patient’s involvement in the trial and will receive a letter with a copy of the study synopsis and 1-page guideline summary for BP thresholds, targets, and treatments relevant for CKD.

### Study Procedures and Data Collection

At baseline, relevant demographic and health behavior information including age, sex, race, smoking, alcohol intake and details of patient’s medical history such as significant CV disease (eg, coronary artery disease, stroke, peripheral arterial disease, heart failure) and medication history (BP-lowering drugs—name, type, dosage, frequency, and duration) will be collected. Relevant clinical details such as body mass index (BMI) will also be recorded. Blood pressures will be measured and recorded following guideline recommendations.^10,11^ Other information that will be collected includes health care use in the past year (physician and/or emergency room visits, and hospitalizations) ascertained through patient self-reports and/or provincial administrative data sources, quality of life (Kidney Disease Quality of Life-36 [KDQOL-36]) and utility measurements (European Quality of life Five Dimension [EQ-5D]); and satisfaction with receiving health care, using the Patient Assessment of Care for Chronic Conditions (PACIC-2.0).^29-32^

Laboratory measurements will be carried out at baseline including serum electrolytes, serum creatinine (and estimated glomerular filtration rate), glycated hemoglobin (HbA1c), and urinary albumin/creatinine ratio (UACR). These measurements will also be taken at 6-months and 1 year.

Assessment of usability and acceptability is critical for all technology-enhanced care interventions to minimize risk of undesired consequences commonly seen post-implementation.^33,34^ End-user input into system design and operation is important throughout the evaluation process to reduce the risk that interventions will be ineffective, unusable, or unsafe. Usability testing will involve assessment of human-computer interaction—specifically, issues related to use, interface, design, function and will also include acceptability of the model of care for the caregivers. We will take a qualitative approach to this process by using focus groups. We plan to recruit 2 focus groups, 1 for patients in the telemonitoring arm and 1 for care providers (case managers and PCPs), with a target sample size of 5 to 8 participants in each group. The first 5 users typically identify 70% of severe usability problems and the first 8 users typically identify 85%; a higher sample size has low incremental yield due to data saturation.^
35
^ Prior to setting up the patient focus group, an advisory group consisting of patients with CKD and hypertension will first be asked to review contents of the focus group questions for relevance and applicability to real-life patients with hypertension and CKD. Focus group questions for the PCPs will be jointly developed by qualitative research experts and the investigators.

Focus groups will be conducted separately for each of the groups (patients and care providers) after 3 months in the study and again before the end of the study (Figure 2). Sessions will be audiotaped, transcribed verbatim and analyzed using the methodology of interpretive description (ID).^36,37^ ID is a methodology developed to generate knowledge about general patterns and themes that could then be applied to inform care for individual patients.^
38
^ Well-established methods will be used to ensure trustworthiness and rigor, including credibility (iterative cycles of engagement), confirmability (audit trails) and transferability (reporting on kidney disease in the rural context).^37,39^ NVivo software application will be used to code and manage qualitative data and to create a filing system and coding database. Transcripts from the first focus group session for each group will be read and re-read to generate an initial codebook. The codebook will be iteratively refined throughout the analysis. Codes will be categorized and analyzed thematically.^
37
^ Patient and clinician data will first be analyzed separately, and then across groups. Patients’ responses regarding usability and acceptability will be analyzed further in relation to care for their BP control. All groups will offer feedback on acceptability of the system and suggestions for improvement for use in patient care.

Trial-based costing will be assessed with the 3-step micro-costing technique of identification, measurement and valuation of relevant health care and non-health care resources using standard methods,^40,41^ with a focus on cost of telemonitoring and case management, health care costs (through linkage with Alberta Health data), and patient-borne costs (patient survey). Thus, the cost-effectiveness (Model A) and cost utility (Model B) of the intervention will be compared against the control using a modified version of a validated economic model used by the team in prior work on HBPT and case management^
42
^ and other chronic diseases.^41-43^ Best practices for economic evaluation will be followed.^41,44-46^ The intervention includes intermittent or one-time costs (eg, devices, treatment algorithm development, patient and health care professional training) and ongoing costs (eg, network and data, case manager time, BP medications). Data captured during the RCT will accurately determine the costs of telemonitoring, case management, and health care use by patients (physician, ER visits, etc.). The change in BP at 1 year, a validated surrogate, will be a key variable in both analyses:

Model A will calculate the cost per decrement in mean BP using a 1-year time horizon and a public health care payer perspective.Model B will estimate incremental cost per quality-adjusted life year (QALY) gained over a lifetime.^42,47^ It will consider longer-term health outcomes, including the probability of developing end-stage kidney disease (ESKD) (requiring dialysis or transplant) or major CV events (ie, coronary artery disease, heart failure, stroke), all-cause mortality, impacts on quality of life (EQ-5D), and health care costs associated with these outcomes.

In each model, we will explore distributions using bootstrapping, create acceptability curves, and perform one-way and probabilistic sensitivity analyses to explore the impacts of uncertainty in key model parameters. In Model B, the potential impact of reducing complications of treating hypertension in patients with CKD (hypotension, syncope) by a plausible range will be explored in a sensitivity analysis using baseline risk determined from a population-based cohort of patients^
48
^ and ambulatory care sensitive conditions^
49
^ for emergency room visits and hospitalizations.

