## Methods

### Study Objectives

The primary aim of this study is to assess the mean difference in SBP at 12 months, from baseline in remote communities in Northern Alberta through a pragmatic RCT, comparing HBPT + usual care versus HBPT + a case manager. Secondary aims of the study will include:

Proportion of patients who maintained home SBP within guideline target (<130 mmHg)^10,11^ from baseline to the end of the study.Proportion of patients who remained within guideline target SBP (<130 mmHg),^10,11^ throughout the study.The user acceptability of HBPT for BP control, using a qualitative approach.The cost-effectiveness and cost utility of HBPT combined with a protocol-based case management approach among remote-dwellers with CKD compared to the usual care.5.Proportion of adverse events, eg, syncope, hypotension requiring assistance or medical attention, worsening of kidney function (2x serum creatinine or 50% decline in estimated glomerular filtration rate [eGFR]), and/or electrolyte abnormalities [hyperkalemia ≥ 6.5 mmol/L], in each arm of the study.

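### The economic aim and cost list do not match the randomised comparison: both arms receive HBPT, so the trial can value only case management added to it

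*Protocol article*

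**What the plan says.** Under Design, Randomization, and Allocation the protocol article gives the randomised comparison as "HBPT plus protocol-based case management versus HBPT plus usual care". The Control arm section adds: "Patients in the control arm (usual care) will receive the same HBPT device and BP measurement training as those in the intervention arm". Controls also follow the same measurement protocol. The note to Figure 3 describes the same wireless transfer to a secure server for patients of both arms. What differs is who acts on the readings: a case manager in the intervention arm, the patient's own primary care provider in the control arm.

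The economic text is worded differently. The fourth secondary aim under Study Objectives is "The cost-effectiveness and cost utility of HBPT combined with a protocol-based case management approach among remote-dwellers with CKD compared to the usual care". Study Procedures and Data Collection then says that "the cost-effectiveness (Model A) and cost utility (Model B) of the intervention will be compared against the control". The costing is planned "with a focus on cost of telemonitoring and case management", together with health care and patient-borne costs. On the make-up of the programme cost it says: "The intervention includes intermittent or one-time costs (eg, devices, treatment algorithm development, patient and health care professional training) and ongoing costs", the ongoing part being illustrated by "eg, network and data, case manager time, BP medications".

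Model A is a one-year cost per unit fall in mean BP from the public payer's side. Model B is a lifetime incremental cost per QALY. Both take the one-year BP change as a key input.

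**The concern.** Read on its own, the economic text describes a trial in which one arm is telemonitored and the other is not. The aim names usual care without HBPT, the cost list assigns the equipment, patient training and data link to the intervention, and the focus-group plan in the same section speaks of a single telemonitoring arm. The Introduction also names the unknown cost-effectiveness of HBPT in remote CKD patients as part of the motivation.

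No randomised arm is without HBPT. Whatever HBPT itself does to BP is present on both sides and drops out of the observed difference. An analyst who costs the intervention from the list as written, and does not give controls the same items, would put the cost of HBPT into the numerator with no corresponding effect in the denominator. The error would run against case management. It would affect a declared secondary outcome that is meant to inform policy.

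**Working it through.** The plan states no economic figure, so there is none to reproduce. The check is to place each listed cost item against what each arm receives, and then write out the increment.

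| Item listed as an intervention cost | Intervention arm | Control arm | Basis |
|---|---|---|---|
| Device | yes | yes, the same | Control arm section |
| Patient BP training | yes | yes, the same | Control arm section |
| Network and data | yes | yes | note to Figure 3 |
| Algorithm development | yes | no | case-manager protocol only |
| Professional training | yes | treated here as no | not described for controls |
| Case manager time | yes | no routine interaction | Control arm section |
| BP medications | yes | yes, amount may differ | eligibility requires current antihypertensive treatment |

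**Notation, per patient.** S is the shared HBPT cost (first three rows). K is the case-management package (algorithm, professional training, case manager time). M1 and M0 are medication and health care costs in the intervention and control arms. D is the between-arm SBP difference in mmHg.

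**Shared costs counted in both arms:** (S + K + M1) − (S + M0) = K + M1 − M0. S cancels.

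**Shared costs charged to the intervention arm only:** (S + K + M1) − M0 = (K + M1 − M0) + S.

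**Model A.** The cost per mmHg rises from (K + M1 − M0)/D to (K + M1 − M0 + S)/D, an excess of S/D. Sample Size Estimation gives 10 mmHg as the difference to be detected between the two arms, so at D = 10 the excess is S/10. S is not given. For assumed values:

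- S = 100 currency units: 100/10 = 10 units per mmHg
- S = 200: 200/10 = 20 units per mmHg
- S = 400: 400/10 = 40 units per mmHg

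If the observed D were below 10, the excess per mmHg would be larger for the same S.

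**Model B.** The incremental cost is too high by S. The effect on the ratio depends on the QALY gain, for which the article gives no figure.

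**Limit of the algebra.** Exact cancellation assumes equal use of S. The measurement week is repeated monthly until BP is at target and three-monthly afterwards, so network and data use could differ somewhat if one arm reaches target sooner. That is a reason to count these items as incurred in each arm, not to assign them to one.

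**The case against.** The strongest reply is that this is loose wording and not a planned error. The Control arm and Sample Size Estimation sections both use usual care as the label for the control arm, and the primary aim in the same section as the economic aim names HBPT on both sides. The operative economic sentence compares the intervention with the control. The cost list also includes BP medications, which controls plainly take, so it can be read as an inventory of components and not as a list of costs unique to one arm. Model B is described as incremental, best practice in economic evaluation is promised, and an article may leave allocation of costs by arm to a fuller document.

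Much of this stands. A valid increment can be estimated from the design, and nothing says that control-arm HBPT costs are set to zero. A reader might infer that the economic aim cannot be answered at all; the article does not support that, because the question of case management added to HBPT is answerable.

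A reader might also infer that EQ-5D is collected only at baseline, since it is listed in the paragraph on baseline data and the sentence "These measurements will also be taken at 6-months and 1 year" follows the laboratory list. That rests on position in a condensed article whose trial-design figure is not shown, and the text nowhere says that EQ-5D is restricted to baseline. Model A does not use EQ-5D, and Model B can run on BP change and modelled events. At most this is a request to print the follow-up time points; it is no part of the finding.

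What the reply does not remove is that the aim, the cost list and the focus-group wording all lean towards a one-armed telemonitoring design, and no sentence says that the shared costs are counted for controls.

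**Conclusion.** The concern holds as an inconsistency between the economic specification and the randomised design. The trial can value case management on top of HBPT; it cannot value HBPT itself, nor HBPT plus case management against care without HBPT. If the list were applied to one arm only, the bias would be S/D per mmHg in Model A and S in Model B's incremental cost, in both cases against the intervention.

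The direction follows from the design. The size rests on S, which the article does not give; the values of 100 to 400 units are illustrations only. A proportional inflation of programme cost cannot be stated either, because the share due to HBPT is not reported. The article does not treat the amount as negligible: Potential Challenges and Mitigation Strategies cites the cost of home monitors as what made similar trials expensive, and allows for the team to supply smartphones and internet access. The primary outcome and the sample size are unaffected.

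**What to change.** Restate the fourth secondary aim with its actual comparator: HBPT plus case management versus HBPT plus usual care. In the costing text, state that device, patient BP training and network/data costs are counted in both arms as incurred. The increment then consists of case-manager time, algorithm development, professional training, and differences in medication and health care use. Describe the patient focus group by the arm it is drawn from, since both arms are telemonitored.

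These are wording changes that can be made before analysis, with no effect on randomisation or sample size. The cost is a narrower economic claim: the result will speak to case management added to HBPT and not to HBPT itself.

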### Potential Challenges and Mitigation Strategies

We have identified potential challenges to this study and have prepared mitigation strategies to address them. First, although the 1-year follow-up period could be considered short, however, longer follow-up period is often desirable when observing hard outcomes (eg, progression to dialysis, time to first / repeat CV event, death, etc.). This follow-up duration was selected as we recognize that BP is a surrogate outcome and is the most important measure for predicting adverse CKD outcomes. Also, it is well established that reducing high BP among patients with CKD substantially reduces complications and risks of adverse events. Avoiding low BP and resultant adverse effects is also important. However, beyond the scope of this study, we will examine how treatment and monitoring affect hospitalization rates, CV events, and mortality over long term. Second, possible technological pitfalls may provide challenges to conducting this study. We note that frequent monitoring and intervening too aggressively may also cause adverse consequences. Such consequences will be minimized by responding to qualitative feedback, standardizing telemonitoring frequency, ensuring careful monitoring for adverse effects and changing drug regimens as necessary. Third, owning a smartphone and having access to wireless internet is an eligibility requirement for this study and could therefore exclude potentially eligible patients who do not have smartphones. However, as more than 85% of Canadians own a smartphone^
53

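### The one Model B scenario named for treatment complications explores only a reduction, although the protocol accepts that the intervention may cause harm

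*Protocol article*

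**What the plan says.** The protocol article, under Study Procedures and Data Collection, describes two economic models. Model B estimates cost per QALY over a lifetime. Its listed long-term outcomes are introduced as "including the probability of developing end-stage kidney disease (ESKD) (requiring dialysis or transplant) or major CV events", followed by mortality, quality of life and costs. Hypotension and syncope are not in that list, although the list is not worded as closed.

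For both models the team will "perform one-way and probabilistic sensitivity analyses to explore the impacts of uncertainty in key model parameters"; the key parameters are not named. For Model B alone the text adds that "the potential impact of reducing complications of treating hypertension in patients with CKD (hypotension, syncope) by a plausible range will be explored", "using baseline risk determined from a population-based cohort of patients". No figure is given for the baseline risk or for the width of the range.

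Three other places bear on direction:

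- Potential Challenges and Mitigation Strategies: "We note that frequent monitoring and intervening too aggressively may also cause adverse consequences".
- Study Objectives, among the secondary aims, for each arm: "Proportion of adverse events, eg, syncope, hypotension requiring assistance or medical attention". Adverse Events and Safety Monitoring lists syncope and hypotension again as safety concerns.
- Discussion: the work is expected to reduce over-treatment and its consequences, syncope included.

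**The concern.** A sensitivity analysis should show how far a conclusion depends on an uncertain input. Whether case management lowers or raises hypotension and syncope is not known before the trial. Medication may go up or down in the intervention arm, and the sample size assumes a mean SBP 10 mmHg lower than under usual care, so either direction is plausible. The article allows for both: it hopes for fewer events in the Discussion and warns of harm under Potential Challenges. The named scenario carries only the hope into the model.

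At stake is the balance of the cost-utility evidence. The findings are meant to support policy and scale-up. A decision-maker who sees complications varied only downward learns how much better the intervention might look, but not how much worse.

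**Working it through.** The article attaches no figure to this scenario, so there is nothing to reproduce. The check has three parts: a sign argument, an illustration of what lies on the unnamed side, and a check of whether the trial could settle the direction.

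**1. Sign of the scenario.** Let r be the baseline complication risk, RR the relative risk under the intervention, c the cost and q the QALY loss per complication, and λ the value of a QALY. Leaving discounting and survival aside, the part of the intervention's incremental net benefit due to complications is

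−r × (RR − 1) × (λq + c).

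With r, c and q not negative, this falls as RR rises. Lowering RR from any base-case value therefore leaves net benefit unchanged or raises it. A range that only lowers RR cannot produce a less favourable result for this parameter. This assumes that the reduction is applied to the intervention arm, which the context implies but the text does not state.

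**2. What lies on each side.** Change in events per 100 patients = 100 × r × (RR − 1). All risks and relative risks here are assumptions.

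| Assumed risk r | RR 0.5 | RR 1.5 | RR 2.0 |
|---|---|---|---|
| 2% | −1.0 | +1.0 | +2.0 |
| 5% | −2.5 | +2.5 | +5.0 |
| 10% | −5.0 | +5.0 | +10.0 |
| 15% | −7.5 | +7.5 | +15.0 |

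Only the RR 0.5 column has the direction that the article names. A range of 0.5 to 2.0 is symmetric as a ratio, but in absolute events its upper side is twice its lower side.

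**3. Can the trial settle the direction?** The arm sizes come from Sample Size Estimation: 58 per arm analysed, or 73 recruited. Assume the same risk p in both arms and an observed risk ratio of 1. With m patients per arm,

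SE of log RR = √[2 × (1/(pm) − 1/m)], and the 95% interval is exp(±1.96 × SE).

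Example with m = 73 and p = 2%: pm = 1.46; SE = √[2 × (0.6849 − 0.0137)] = 1.159; the interval is 0.10 to 9.7.

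| m per arm | p = 2% | p = 15% |
|---|---|---|
| 73 | 0.10–9.7 | 0.46–2.2 |
| 58 | 0.08–12.8 | 0.42–2.4 |

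Over the same assumed risks, power to detect a doubling is about 10% to 59% with 73 per arm and 9% to 49% with 58. A doubling would stay inside every one of these intervals, so the trial alone would probably not rule out an increase.

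**The case against.** The strongest reply is that this is one scenario among several. The sentence before it plans one-way and probabilistic analyses of unlisted parameters in each model, and complications may be among them, varying either way. Harm seen in the trial also has other routes into the evaluation: "Data captured during the RCT will accurately determine the costs of telemonitoring, case management, and health care use by patients", and EQ-5D feeds Model B. This stands. A reader might infer that Model B as a whole can only favour the intervention, that an increase will never be examined, or that the trial's own data are ignored. The document supports none of these.

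A reader might also infer that the base case becomes the worst case by construction. That does not follow either. The base-case value is not stated, and a base case that carries observed health care use could already contain harm.

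A second reply is that a journal article leaves ranges to a fuller plan. That excuses the missing width but not the direction, which the article does state.

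Third, exploring fewer complications is a legitimate test of the hypothesis in the Discussion, and the warning about aggressive intervention is followed at once by measures to limit such harm. Both are fair. But mitigation lowers the chance of harm without fixing its sign, and a test of the hoped-for direction does not replace a test of the other.

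Finally, an external cohort is a reasonable source for baseline risk, given how few events this trial may yield. That is not a fault.

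**Conclusion.** The point holds for the one named scenario. As worded, it varies hypotension and syncope downward only, although the article itself allows that harm may rise and measures these events by arm. The wider sensitivity analyses may fill the gap, but the text does not say that they do.

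The effect on cost per QALY cannot be sized from the document: complication risk, unit cost, utility loss and the duration over which complications are modelled are all absent. The event counts above are illustrations on assumed risks. The conclusion rests on two assumptions: that the reduction is applied to the intervention arm, and that a complication never saves money or gains QALYs. It is confined to the cost-utility part of a secondary outcome. The primary SBP comparison, its power and the by-arm analysis of adverse events are untouched.

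**What to change.** In the Model B sentence, replace *reducing* with *changing*. Vary the relative risk of hypotension and syncope on both sides of 1 in the one-way analysis; 0.5 to 2.0 would serve as an example, and is an assumed range. Include the same parameter in the probabilistic analysis, with a distribution that allows an increase. That distribution should be informed by the trial's between-arm estimate and carry its full uncertainty. The point estimate alone would be too imprecise to rely on. The external cohort may still supply the baseline risk. State to which arm the change is applied and what the base-case value is.

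The cost is one extra parameter range in an existing model, with no new data. The cost per QALY may look less favourable in part of the range.
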